**Table 1 Tab1:** **Outcome measures and time points**

Outcome measure	Part of study		Time point (weeks)		
	Part one	Part two	0	6	12
Shoulder Pain and Disability Index	Yes	Yes	Yes	Yes	Yes
Impact and costs questionnaire	Yes		Yes		
Work Productivity and Activity Impairment Questionnaire	Yes		Yes		
Work Limitations Questionnaire	Yes		Yes		
Usual waiting time	Yes		Yes		
Examiner agreement	Yes		Yes		
European Quality of Life, five dimensions, five levels	Yes	Yes	Yes	Yes	Yes
Pain severity visual analogue scale	Yes	Yes	Yes	Yes	Yes
Range of movement/pain pre- and post-injection		Yes	Yes		
Adverse events		Yes	Yes, throughout		
Global perceived improvement		Yes	Yes	Yes	Yes
Satisfaction visual analogue scale		Yes			Yes
Post-injection physiotherapy		Yes			Yes
Labour costs		Yes			Yes
Medicine use	Yes	Yes			Yes

The table indicates which outcome measures will be used in each part of the trial and when each outcome measure is collected.

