### Secondary outcome measures

#### Economic disease burden at baseline

An impact and costs questionnaire has been developed to gather shoulder-related direct and indirect costs including medical care, work earnings, impact and absence, and also costs of personal assistance required from others. A 3-month recall period was chosen based on previously reported patient accuracy in recall over this period
[30, 31]. Impact on work productivity will be further assessed with two work productivity instruments which are validated in this patient population
[32]. The Work Productivity and Activity Impairment Questionnaire has been used in many musculoskeletal conditions, is compatible with economic costing, and is easy to administer. The Work Limitations Questionnaire
[33] is a widely used presenteeism measure with excellent construct validity and the benefit of being expressed as a percentage of productivity loss for dual clinical and economic analyses.

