#### Post-injection physiotherapy

The number of physiotherapy sessions provided for post-injection participants will be obtained from hospital booking systems.

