### Data analysis

All statistical analyses will be performed on an intention-to-treat basis with alpha level set at 0.05. As suggested in an extension of the CONSORT statement for non-inferiority trial design
[45, 46], per-protocol analysis will be conducted and the results obtained by the two approaches will be compared
[47].

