#### Economic evaluation

A within-trial economic evaluation, adhering to current guidelines
[53], will be undertaken from the perspective of the health funder. A cost-utility ratio will be constructed using the formula: cost-utility = (Cost_i – Cost_c) /(QALY_i – QALY_c), where: QALY = quality-adjusted life years calculated by mapping the EQ-5D-5 L utility score across time and calculating the area under the curve, i = intervention group for main effect analysis, and c = control group. The time horizon for this economic evaluation will be 12 weeks. Direct costs will include labour costs of the clinician providing the injection, post-injection physiotherapy and change in medicine usage. Univariate, multivariate and probabilistic sensitivity analyses will be conducted to confirm stability of results and adjust for uncertainty in clinical and economic data.

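### The cost-utility analysis takes a 12-week health-funder perspective, but further shoulder care after the injection is neither reliably recorded nor costed

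*Protocol article*

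**What the plan says.** Under Economic evaluation, the analysis "will be undertaken from the perspective of the health funder", and "The time horizon for this economic evaluation will be 12 weeks". The cost side is then specified: "Direct costs will include labour costs of the clinician providing the injection, post-injection physiotherapy and change in medicine usage".

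The sections on resource use match that list. Under Post-injection physiotherapy, "The number of physiotherapy sessions provided for post-injection participants will be obtained from hospital booking systems". Under Costs, staff time is priced from wage scales and medicines from the Pharmaceutical Benefits Scheme.

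Medical care more broadly appears only under Economic disease burden at baseline: "An impact and costs questionnaire has been developed to gather shoulder-related direct and indirect costs including medical care". In Table 1 the row "Impact and costs questionnaire" is marked for Part One and week 0. It is not marked for Part Two, week 6 or week 12. On its recall window the protocol says: "A 3-month recall period was chosen based on previously reported patient accuracy in recall over this period".

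**The concern.** A health funder pays for more than the injector's time, hospital physiotherapy and medicines. A participant who does poorly may see a GP or the specialist again, have more imaging, receive a second injection, or attend physiotherapy elsewhere. Such contacts fall within the 12-week horizon and, where publicly funded, within the stated perspective. The plan neither asks about them after injection nor lists them as costs.

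Two results are affected. The first is the cost-utility ratio, a secondary aim: its numerator is wrong by whatever difference in uncounted care exists between the arms. The second is the interpretation of the primary outcome. If one arm receives more further care and benefits from it, the 12-week SPADI difference reflects injection plus that care, and the reader has no data by arm to see this. The Discussion notes that the two injectors differ in recency and frequency of practice, so a difference in subsequent care is conceivable, although the protocol gives no evidence of one.

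**Working it through.** **Step 1. Compare perspective, cost list and data sources.**

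| Funder cost after injection | Listed as a direct cost? | Post-injection data source in the protocol |
|---|---|---|
| Injector's time | Yes | Wage scales |
| Hospital physiotherapy | Yes | Booking systems |
| Medicines | Yes (change in use) | Assessor's record, Table 1 week 12 |
| Repeat injection | No | None designed for it; the medicine record might catch some |
| GP or specialist visit | No | None designed for it; adverse-event reports might catch some surgeon contacts |
| Imaging | No | None |
| Physiotherapy outside the hospital | Not captured by the stated source | None |

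The cost list and the measurement table agree with each other. Both are narrower than the stated perspective.

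**Step 2. Form of the cost bias.** Let p_P and p_S be the mean number of uncounted care episodes per participant in the physiotherapist and surgeon arms, and c the funder's price of an episode. The incremental cost is wrong by (p_P − p_S) × c. This is zero if use is equal, and it can take either sign. None of the three inputs is in the protocol.

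As an assumed example only, take a difference of 3 episodes in 32 participants and a price of A$200 to A$400:
- 3/32 × 200 = A$18.75 per participant
- 3/32 × 400 = A$37.50 per participant

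The figure is added to the physiotherapist arm's cost or taken from it, according to which arm used more care.

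**Step 3. The protocol's own sample size, whose inputs are used in Step 4.** With SD 21.7, margin 15, one-sided alpha 0.05 and 80% power, n per arm = 2 × 21.7² × (1.645 + 0.842)² / 15² ≈ 25.9, so 26. With the t distribution, 27 per arm gives 80.6% power and 26 gives 79.2%, so the stated 54 is reproduced. After 15% drop-out, 54/0.85 = 63.5, so 64. Nothing in this point alters those figures.

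**Step 4. What further care could do to the SPADI comparison.** If an excess share e of the physiotherapist arm has further care and each such participant gains b points, the observed difference shrinks by e × b. Suppose the difference without that care equals the 15-point margin. The standard error is 21.7 × √(2/27) = 5.91, and the chance of declaring non-inferiority is Φ(e × b / 5.91 − 1.645). Both e and b are assumptions; b runs from 15 to 23.1 points, the margin and the minimum clinically important difference in the Sample size section.

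| Excess share e | Shift e × b (points) | Chance of declaring non-inferiority |
|---|---|---|
| 0 | 0 | 5% |
| 5% | 0.75 to 1.16 | 6.5 to 7.4% |
| 10% | 1.5 to 2.31 | 8.2 to 10.5% |
| 20% | 3.0 to 4.62 | 13 to 19% |

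If the excess were in the surgeon arm, the shift would run the other way. The table shows sensitivity; it is not an estimate for this trial.

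**The case against.** Several counter-arguments carry weight.

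- **The wording may not be exhaustive.** The cost sentence could be read as giving examples, and a journal article condenses. However, the article prints a complete measurement table and a specific cost list, and they match. Widening the list later would not supply follow-up data that were never collected. The planned sensitivity analyses would likewise have no trial data on these items to vary.
- **Part of the cost of a poor result is captured.** Physiotherapy sessions are at the treating physiotherapist's discretion and are costed, as is change in medicine use. Worse health also enters the QALYs through the EQ-5D-5L at 0, 6 and 12 weeks. This stands. It would be too strong to say that the cost of a failed injection is left out altogether; consultations, procedures, imaging and outside physiotherapy are what is missing.
- **The omission applies to both arms.** A reader might infer that the cost comparison is tilted by design towards the injector with the lower wage. The protocol does not support that. The direction depends on which arm uses more further care, which is unknown.
- **The per-protocol analysis is not shown to be defeated.** A reader might also infer that retreated participants had to be removed from that analysis and cannot be identified. The Data analysis section says only that "per-protocol analysis will be conducted and the results obtained by the two approaches will be compared"; it states no rule on retreatment, and the definition of the set may properly sit in the analysis plan. Some repeat injections might surface through the medicine record. Excluding retreated participants would also select on a response to a poor result: it would remove failures from the worse arm and could itself favour non-inferiority.
- **Intention-to-treat remains legitimate.** Counting outcomes whatever further care follows is a valid comparison of treatment policies. This too stands. What is missing is information to interpret it.

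**Conclusion.** The point holds for the economic evaluation. As written, the plan claims a 12-week funder perspective but neither reliably records nor costs further consultations, repeat procedures, imaging and outside physiotherapy after injection. The cost-utility ratio is biased if that care differs between arms, in either direction. For the primary outcome the consequence is weaker: the SPADI analysis is not invalid, but it cannot be read against the further care each arm received.

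The size cannot be derived from the protocol. Every retreatment rate, gain and price in the worked examples is an assumption. With an excess of 5% in the physiotherapist arm the effect on the non-inferiority error is small; the larger values need excesses that nothing in the protocol suggests. The change is worth making because it is cheap, not because a large bias has been shown.

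**What to change.** 1. Repeat the health-care-use items of the existing impact and costs questionnaire at the 12-week assessment, worded to cover the period since the injection. The 3-month recall fits that interval. Cover further injections, GP and specialist visits, imaging, and physiotherapy outside the hospital, and add the row to Table 1 for Part Two at week 12.
2. Add these items, with unit costs, to the direct costs under Economic evaluation.
3. Report further injections and other shoulder care by arm, as a descriptive result or sensitivity analysis beside the SPADI comparison. Do not exclude retreated participants from the per-protocol set on this basis.

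The cost is slightly more participant time at a contact that already takes place, a few more unit costs and a short amendment. Recruitment began in January 2013, so participants already followed up could be covered only in part, from hospital records; the report should say how many lack the questionnaire data.

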## Discussion

The findings of this study will provide further evidence informing policy makers, regulators, health professionals, and the public as to the feasibility and safety of appropriately trained physiotherapists in Australia in requesting prescribing and administering medicines. The model of care to be evaluated in this study has the potential to reduce waiting times and improve access to appropriate and expedited care for patients who presently face long orthopaedic waiting times for specialist orthopaedic services. We anticipate this will have subsequent effects in improving patient flow, which could ultimately benefit both surgical and non-surgical orthopaedic pathways. The results may also have application for the management of other musculoskeletal presentations.

A non-inferiority randomised controlled trial design was chosen as it is appropriate when comparing an alternative treatment with an established proven effective treatment for a condition, and it is hypothesised that the alternative will not be superior in efficacy to the established treatment. In this case the objective is to determine whether the alternative treatment (physiotherapist injection) is not inferior to the existing gold standard (orthopaedic surgeon injection). This is done by assessing whether the alternative treatment falls within the non-inferiority margin
[54].

This study will be limited by its involvement of only one injecting physiotherapist. This is necessary because there is presently no regulatory framework, recognised training curriculum or accreditation process for Australian physiotherapists to prescribe or administer medicines by injection. The physiotherapist in this study obtained governance approvals on the basis of their overseas training and is not representative of other physiotherapists in Australia. If physiotherapist-led prescribing and injecting were to be implemented on a wider scale, appropriate training and regulatory frameworks would be required.

Further potential limitations of the study include differences in practice recency and frequency between the surgeon and the physiotherapist, as governance approvals permit the physiotherapist to inject only within the trial. In contrast the surgeon has recent practice and will have regular ongoing injection practice through their work outside of the research.

In summary, several knowledge gaps will be addressed by this research. It will evaluate the safety, feasibility, and cost of physiotherapists injecting in an Australian setting. To our knowledge, it will also, for the first time, compare the decision-making processes and clinical efficacy surrounding injection by a physiotherapist to that of a consultant orthopaedic surgeon, for a specific orthopaedic condition. We believe this to be the first study of a physiotherapist injecting corticosteroid in Australia, and it could serve as a benchmark from which subsequent studies can be conceived to further our understanding of the potential health benefits of extended-scope activity within physiotherapy, as well as other allied health professions.

## Trial status

Recruitment began in January 2013, with the first participant randomized 16 January 2013.

## Abbreviations

EQ-5D-5 L: European quality of life (five dimensions, five levels)
GEE: Generalised estimating equation
GP: General practitioner
SPADI: Shoulder Pain and Disability Index
VAS: Visual analogue scale.
